## **7. Analysis populations**

### **Full Analysis Set (FAS)**

Based on the principles of Intention-to-Treat analysis (ITT), all randomized subjects, either treated with medication or with EVT will be included in the full analysis set. The primary effectiveness endpoint analysis of this study will be performed on the FAS.

### **Per Protocol Set (PPS)**

The PPS is a subset that includes all subjects who were treated with the treatment to which they were randomized and there are no clinically meaningful deviations from the protocol. Severe derivations from the protocol will be finally defined during the data auditing process, including but not limited to the followings:

- 1) The subject is not in line with the inclusion criteria.
- 2) There exist other treatments that potentially confound the appraisal of efficacy of the planned treatment.
- 3) Poor compliance.
- 4) Follow-up interval exceeds the required time window.

Secondary analysis will be conducted on the PPS, whenever its result is not consistent with the one from the FAS, a detailed analysis of the difference is needed.

---

## **Safety Analysis Set (SAS)**

The safety analysis set consists of all subjects who received treatment with at least one time evaluation of safety outcome.

## **8. Treatment comparisons**

The treatment comparison of interest in this study is to assess the safety and efficacy of best medical management plus EVT compared to best medical management alone in patients with AIS due to LVO in anterior circulation up to 24 hours from symptom onset or last seen well.

## **9. General considerations for data analyses**

All analyses will be performed using SAS Version 9.4. All analysis output will use the treatment group naming of best medical management plus EVT group and best medical management group. All statistics were two sided with a  $P < 0.05$  considered significant.

### **Examination of Subgroups**

The extent to which the treatment effect of improvement in modified Ranking scale varies across levels of each subgroup will be assessed through interaction tests.

### **Multiple Comparisons and Multiplicity**

A single primary efficacy variable has been defined for this study, with all other efficacy variables identified as secondary or other. Similarly, only one treatment comparison is of interest in the study and therefore there are no requirements to adjust for multiple comparisons or multiple endpoints within this study.

---

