## 3. Study Endpoint(s)

Primary Efficacy Endpoints:

The 90 ( $\pm 7$ ) day modified Ranking scale.

Secondary Efficacy Endpoint:

- 1) 90 ( $\pm 7$ ) day mRS 0-2.
- 2) 90 ( $\pm 7$ ) day mRS 0-3.
- 3) 36h (24-48h) NIHSS 0-1 or decrease  $\geq 10$  from baseline.
- 4) 36h (24-48h) infarct volume change (by CT or MRI).
- 5) 36h (24-48h) target artery recanalization rate (by CTA or MRA).

---

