#### **Main Model**

Based on an intention-to-treat basis, an ordinal logistic regression model with site as a random effect will be used to calculate the common odds ratio between the two treatment groups. If the proportional odds assumption for ordinal logistic regression were not satisfied, the Wilcoxon-Mann-Whitney generalized odds ratio will be calculated using assumption-free ordinal analysis. All statistics will be two-sided with  $p < 0.046$  considered significant.

---

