## Interactions with Subgroups

Summary tables will be produced for the predefined subgroups and interactions between treatment and these subgroups will be investigated, using an ordinal logistic regression model. A separate model will be used for each interaction to determine its significance. This will also be presented graphically on a forest plot.

The predefined subgroups including:

- Age ( $< 75$  vs.  $\geq 75$ )
- Weak-up stroke or not
- Last known well to randomization time ( $< 6h$  vs.  $\geq 6h$ )
- Stroke severity before randomization (NIHSS $<16$  vs. NIHSS $\geq 16$ )
- Intravenous thrombolysis or not
- Occlusion site (ICA vs. M1 segment)
- Ipsilateral carotid artery occlusion or not
- ASPECT score ( $< 3$  points vs.  $\geq 3$  points)
- Infarct core volume ( $< 70ml$  vs.  $\geq 70ml$ )
- Etiological stroke subtype (cardiac embolism vs. large artery atherosclerosis)

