## Secondary Efficacy Analyses

### 90-day mRS 0-2

The proportion of 90-day mRS 0-2 will be analyzed using a binary logistic regression model with site as a random effect. The odds ratio with 95% CI will be reported.

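### One primary endpoint does not remove multiplicity for the secondaries and subgroups: SAP v2.0 applies a blanket significance threshold to five secondary endpoints and ten interactions, with no order, gate or exploratory label

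*Supplement*

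**What the plan says.** The latest SAP (v2.0) deals with multiplicity in section 9. It notes that there is a single primary efficacy variable, "with all other efficacy variables identified as secondary or other", and a single treatment comparison, and it concludes that "therefore there are no requirements to adjust for multiple comparisons or multiple endpoints within this study".

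Two thresholds are given, both worded to cover everything:

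- Section 9, general considerations: "All statistics were two sided with a $P < 0.05$ considered significant".
- Section 12, Main Model: "All statistics will be two-sided with $p < 0.046$ considered significant". Protocol V7.1 section 10.3.2 also gives 0.046, in its primary efficacy paragraph.

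The analyses within reach of these sentences are:

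- **Five secondary efficacy endpoints** (section 3): 90-day mRS 0-2, 90-day mRS 0-3, NIHSS response at 36 h, infarct volume change, and target artery recanalisation. Section 12 gives each its own between-arm analysis, for example "The proportion of 90-day mRS 0-2 will be analyzed using a binary logistic regression model with site as a random effect". Four of the five are to be reported as odds ratios with 95% CIs. Infarct volume change is specified only as a t-test or Wilcoxon test.
- **Ten subgroup interactions** (section 12): "A separate model will be used for each interaction to determine its significance".

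Neither SAP v2.0 nor protocol V7.1 gives a test order, makes the secondaries conditional on the primary, divides alpha, or calls the secondary or subgroup analyses exploratory. Protocol section 10.3 leaves the definition of the planned analyses to the SAP.

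**The concern.** Having one primary endpoint is a good reason not to adjust the primary test. It says nothing about results beyond the primary that the plan also allows to be called significant. Section 9 moves from the first statement to the second without a further argument.

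Read literally, the plan lets a secondary endpoint or a subgroup interaction be called significant when the primary is not, and it does not say how such a result should be read. This matters most for two kinds of result. The first is mRS 0-2, which SAP section 6 also uses as the interim efficacy variable, so a nominally significant result there would carry weight. The second is the set of interactions on time window, ASPECTS and core volume, which bear on which patients are thought to benefit.

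**Working it through.** **The plan's own figures.** The documents state no family-wise error for the secondary or subgroup tests, so there is nothing of that kind to reproduce. For the primary, simulating the levels 0.0002, 0.0123 and 0.046 at 168, 336 and 502 patients gives an overall two-sided error of 0.0498. This treats the three looks as one accumulating statistic. The primary is therefore set aside.

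**Inputs.** Level per test: 0.05 (SAP section 9) or 0.046 (SAP section 12, Main Model). Number of tests: k = 5 (section 3) and k = 10 (section 12). The correlation between test statistics is not in the documents. It is assumed, with a range from 0 to 0.8.

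**Formulas.** All nulls are true and tests are two-sided at level α.

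- Independent tests: P(at least one) = 1 − (1 − α)^k.
- Common correlation ρ: P(at least one) = 1 − ∫ φ(f) [Φ((c − √ρ f)/√(1−ρ)) − Φ((−c − √ρ f)/√(1−ρ))]^k df, with c = 1.960 for 0.05 and 1.995 for 0.046.

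**Results.**

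| Family | Level | ρ = 0 | ρ = 0.5 | ρ = 0.8 |
|---|---|---|---|---|
| 5 secondaries | 0.05 | 1 − 0.95^5 = 22.6% | 18.3% | 12.7% |
| 5 secondaries | 0.046 | 1 − 0.954^5 = 21.0% | 17.0% | 11.8% |
| 10 interactions | 0.05 | 1 − 0.95^10 = 40.1% | 28.7% | 17.3% |
| 10 interactions | 0.046 | 1 − 0.954^10 = 37.6% | 26.8% | 16.1% |

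**Without recanalisation.** A true effect of EVT on recanalisation is expected, so a significant result there would probably not be false. Four independent secondaries at 0.05 give 1 − 0.95^4 = 18.5%.

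**Check with simulated null trials.** The trials had 452 patients and the plan's control mRS distribution (3, 4, 10, 17, 16, 12 and 38%). mRS 0-2 and mRS 0-3 were taken from the same mRS value. Correlations and subgroup prevalences were assumed.

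- Over four correlation structures of 4,000 trials each, at 0.05, at least one secondary was significant in 16-23% of trials and at least one interaction in 29-39%. At 0.046 the ranges were 14-21% and 27-37%.
- For the secondaries at 0.05, a false result in one given direction occurred in about 9-13% of trials.
- In a further set with latent outcome correlation 0 to 0.5, a secondary was significant at 0.05 while the primary was not significant at 0.046 in 17-18% of trials.

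**The case against.** The strongest reply is that SAP section 4 states one hypothesis, section 9 labels everything else as secondary or other, and the decision not to adjust is disclosed. Nothing in the plan says that a secondary or a subgroup can establish efficacy. Four of the five secondaries already carry odds ratios with 95% CIs, and their paragraphs contain no significance verdict. The subgroups are prespecified and use interaction tests, which is sound practice.

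Much of this stands. Leaving secondaries unadjusted is acceptable when their status is stated. The plan does not state it: it attaches a threshold to all statistics, says that no adjustment is required, and has the interaction models decide significance. A label of secondary ranks the endpoints without limiting what may be claimed from them.

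Two stronger readings are tempting, and the documents do not support them.

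- A reader might infer that the primary conclusion is exposed. It is not, because the number of secondary and subgroup tests has no bearing on the primary test's error.
- A reader might pool all 15 tests and quote 1 − 0.95^15 = 53.7%. That figure mixes between-arm comparisons with effect-modification tests. It assumes independence although two secondaries come from the same mRS value, and it counts recanalisation as a true null. Most of it comes from the interactions. The two families are better reported apart.

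**Conclusion.** The point holds in limited form. Section 9's conclusion is valid for the primary and is carried over to endpoints it does not cover. At 0.05 per test with all nulls true, the chance of at least one false positive is about 13-23% for the five secondaries and about 17-40% for the ten interactions. The lower ends need a common correlation of 0.8, and the upper ends need independence. Using 0.046 lowers the figures by about 1 to 3 percentage points and does not change the conclusion. The four safety endpoints are not counted.

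The conflict between 0.05 and 0.046, each stated for all statistics, has to be reconciled in any case. What is at stake is which secondary and subgroup results may be called significant, so this is a change that should be made but does not threaten the trial's main result.

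**What to change.** 1. **Significance sentences.** In SAP section 9, limit the sentence to the primary analysis, with a final two-sided level of 0.046. Limit the Main Model sentence in section 12, and its counterpart in protocol section 10.3.2, in the same way, so that one level applies to one analysis.
2. **Multiplicity paragraph in section 9.** Replace it with a statement that only the primary comparison is confirmatory. Then choose one of two routes for the secondaries:
   - test them in a prespecified order, only if the primary is significant, each at a level no larger than the primary's, stopping at the first non-significant result; or
   - report them as estimates with unadjusted 95% CIs and make no significance claims.

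   Either is enough. If the first is chosen, the investigators should set the order on its merits; the documents give no reason to treat the order of the list in section 3 as the test order.
3. **Subgroups in section 12.** Replace the wording that has each model decide significance with a statement that the interactions are exploratory and are shown as estimates with CIs, unadjusted for multiplicity.

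The cost is SAP wording and a matching line in the protocol; no data, patients or models change. An isolated secondary or interaction can no longer be called significant on its nominal p-value. Under the ordered route, an endpoint placed after a non-significant one loses its formal test.

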## 10. Data handling conventions

### Premature Withdrawal and Missing Data

If any subject withdraws prematurely from the study (prior to the final visit D90±7 days assessment), they are required to complete the withdrawal visit in the CRF. The reasons for withdrawal will be presented in a summary table. For the purposes of summaries and analysis of clinic visit data, this visit will be assigned to the next scheduled clinic visit for that subject, regardless of whether the date falls within the next visit window.

Subjects who withdraw before the end of the study, but who do provide at least one post-baseline measure for a particular endpoint, will be included in the analysis. Subjects who do not attend any visits after randomization will be excluded from analysis of any endpoint, as no post-baseline data will be available.

Outlier values will be evaluated for their validity; all data will be included unless judged to be invalid (e.g., deemed incompatible with life by Medical Monitor and/or deemed invalid by the DSMB).

Efforts will be undertaken at study sites to reduce the amount of missing data. Due to the severity of the condition and the short 90-day follow-up period, very little loss to follow-up is anticipated. For the primary efficacy endpoint, complete data will be used and missing data will not be imputed in the main analysis. Also, sensitivity analyses with missing data imputed by LOCF (Last Observation Carry Forward) and WCCF (Worst Case Carry Forward) methods will be undertaken to explore the effect of missing data on the endpoint and test the robustness of the estimate.

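### The SAP's no-visit exclusion contradicts its all-randomised analysis set and, read literally, drops early deaths; its withdrawal-visit rule conflicts with the 90±7-day endpoint and the no-imputation rule

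*Supplement*

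**What the plan says.** The handling rules are in SAP v2.0, section 10 (Premature Withdrawal and Missing Data).

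- **Exclusion.** "Subjects who do not attend any visits after randomization will be excluded from analysis of any endpoint, as no post-baseline data will be available".
- **Withdrawal visit.** For clinic-visit data from a patient who withdraws before the day-90 assessment, "this visit will be assigned to the next scheduled clinic visit for that subject", even when its date lies outside that visit's window.
- **Inclusion of withdrawals.** A patient who withdraws but has "at least one post-baseline measure for a particular endpoint, will be included in the analysis".
- **Primary endpoint.** "For the primary efficacy endpoint, complete data will be used and missing data will not be imputed in the main analysis".
- **Sensitivity.** "sensitivity analyses with missing data imputed by LOCF (Last Observation Carry Forward) and WCCF (Worst Case Carry Forward) methods will be undertaken".

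These have to be read with the following:

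- SAP section 7: "all randomized subjects, either treated with medication or with EVT will be included in the full analysis set".
- SAP section 12 (Main Model) analyses the primary endpoint by intention to treat, with ordinal logistic regression.
- SAP section 3 defines the primary endpoint as the mRS at 90±7 days.
- SAP section 5 puts the first assessment after randomisation at 36 (24–48) hours.
- Protocol v7.1 Appendix Table 1 scores death as 6 on the mRS.
- Protocol 9.3 requires every serious adverse event to be recorded, and 9.5.3 continues follow-up at the scheduled times after a patient withdraws.

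**The concern.** The exclusion and the Full Analysis Set cannot both be applied. A programmer who follows section 10 removes randomised patients; one who follows section 7 keeps them.

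The practical danger is early death. A patient who dies before the 24–48 h assessment attends no visit, so the words of the rule catch that patient. The reason the rule gives, that there are no post-baseline data, is untrue of a death, which is a complete observation at the worst level of the scale. Because the rule covers any endpoint, it would also take the patient out of 90-day mortality, out of symptomatic haemorrhage within 48 h (where an early fatal bleed is exactly the event sought), and out of the worst-case sensitivity analysis that might otherwise expose the problem.

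The withdrawal-visit rule raises a smaller, separate question: whether an mRS taken well before day 83 can stand as the day-90 value in an analysis that is said to use complete data without imputation.

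**Working it through.** **1. The rules side by side**

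| Patient | SAP section 10 | What it conflicts with |
|---|---|---|
| Attends no visit after randomisation | Out of every endpoint | All-randomised FAS (section 7); intention to treat (section 12) |
| Dies before the 24–48 h visit | Same rule; no exception written | The same, plus death = mRS 6 (protocol Appendix Table 1) |
| Withdraws before day 30, with a withdrawal visit | Value moved to day 30 or an earlier visit | Does not reach the day-90 slot |
| Withdraws between day 30 and day 90, with a withdrawal visit | Value moved to day 90 | 90±7-day endpoint (section 3); no imputation (section 10) |

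The no-imputation sentence conflicts only with the last row. Leaving out patients who truly have no data is what a complete-case analysis does.

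**2. The plan's own figure**

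Inputs (SAP section 6): control mRS 0–6 of 3, 4, 10, 17, 16, 12 and 38%; common OR 1.73; two-sided α 0.046; power 0.90; 1:1 allocation. Whitehead's formula:

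N = 12(z₁₋α/₂ + z₁₋β)² / [(ln OR)² (1 − Σp̄ᵢ³)]

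The EVT distribution implied by OR 1.73 is 5.1, 6.4, 14.6, 21.0, 16.3, 10.5 and 26.2%, so Σp̄ᵢ³ = 0.0475.

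N = 12(1.995 + 1.282)² / [0.3004 × 0.9525] = 450.3, against 452 stated. Attrition: 452/0.9 = 502.2, against 502. The plan's figure is reproduced, and keeping all randomised patients does not change it.

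**3. Effect of dropping early deaths when there is no true effect**

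Both arms have the control distribution (38% dead). An assumed percentage of each arm is taken out of the mRS 6 cell, and the common OR is fitted by maximum likelihood to the expected counts, without the site effect. The early-death percentages are assumptions.

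| Dropped, EVT | Dropped, BMM | Common OR (truth 1.00) |
|---|---|---|
| 2% | 0% | 1.041 |
| 3% | 1% | 1.042 |
| 5% | 2% | 1.066 |
| 5% | 1% | 1.088 |
| 2% | 2% | 1.00 |
| 1% | 3% | 0.96 |

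For 5% against 1%, apparent mortality is (38 − 5)/95 = 34.7% with EVT and (38 − 1)/99 = 37.4% with BMM, when the truth is 38% in both. With a true OR of 1.40, the first four rows give 1.467, 1.474, 1.519 and 1.549; equal loss of 2% gives 1.411.

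**4. The same at the planned effect**

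With 226 per arm there are 0.38 × 226 = 86 control deaths and 0.262 × 226 = 59 EVT deaths. With none dropped, this fit gives power 0.896. Here the assumption is the share of deaths dropped.

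| Share of deaths dropped | Common OR (truth 1.73) | Power |
|---|---|---|
| 5–20%, both arms | 1.725–1.707 | 0.888–0.862 |
| 10–20%, control only | 1.61–1.49 | 0.79–0.63 |
| 10–20%, EVT only | 1.85–1.99 | 0.95–0.98 |

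The result depends on the imbalance between arms much more than on the total lost.

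**The case against.** The best case for the plan is that section 10 deals with withdrawal and missing data and never mentions death. Its stated reason for the exclusion does not fit a death, and deaths are captured without a visit: as serious adverse events, as narratives, and in a Cox analysis of 90-day mortality on the safety set, which is defined by treatment and one safety evaluation. So a sensible analyst would score an early death as 6. This stands as a statement about intent. It does not remove the problem, because the exclusion is written without exception, and for patients who are alive but unseen the clash with the all-randomised set remains.

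On the withdrawal visit, the rule is limited to clinic-visit data, and protocol 3.3 lists day 30 and day 90 as telephone visits. The sentence specific to the primary endpoint could be read as overriding the general rule, and a separate LOCF analysis would be largely redundant if withdrawal values already filled day 90. Follow-up also continues after withdrawal (protocol 9.5.3). Against this, protocol 8.4 allows these visits in person, and the rule is triggered by withdrawal before the day-90 assessment. What stands is a conflict between sentences, not proof that the main analysis carries values forward.

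It is also fair to say that LOCF and worst-case imputation are legitimate prespecified sensitivity analyses. Preferring multiple imputation is a choice of method.

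**Conclusion.** The exclusion is wrong as written: it contradicts the SAP's own analysis set and intention-to-treat model, and its literal consequence is that deaths before 24–48 h vanish from the efficacy and safety endpoints and from the worst-case check. The withdrawal-visit rule conflicts with the endpoint window and the no-imputation sentence for withdrawals between day 30 and day 90. Both should be settled before database lock.

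The size and direction of bias are unknown, because the documents give no early-death rates. On the assumptions shown, a null OR moves to 1.04–1.09 if EVT loses more early deaths, stays at about 1.00 if losses are equal, and falls to 0.96 at 1% against 3%.

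A reader might infer more than this; the documents do not support it:

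- **That the sponsor decided to drop deaths.** The SAP lacks a rule for them; it states no such decision.
- **That the bias favours EVT.** That follows only from assuming more early EVT deaths. Control-only loss works against EVT.
- **That up to 50 patients (502 − 452) could have a relabelled day-90 mRS.** The 10% is a planning allowance, the SAP expects very little loss, and only withdrawals after day 30 with a withdrawal visit would move to day 90.
- **That the exclusion breaches the no-imputation rule.** It does not.

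**What to change.** Amend SAP section 10 as follows:

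1. Delete the no-visit exclusion, so that all randomised patients stay in the Full Analysis Set.
2. Score any death up to the day-90 assessment as mRS 6, whatever visits were attended, and count it in 90-day mortality.
3. State that withdrawal-visit values are not used as the day-90 mRS in the main analysis. Only an mRS obtained within 90±7 days, or death, counts.
4. Let patients with no outcome data enter the sensitivity analyses.

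Multiple imputation using the scheduled day-7 and day-30 mRS, or a tipping-point analysis with shifts that differ by arm, may be added but is optional.

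The cost is a few sentences and a little programming. No new data are needed, and the planned 452 evaluable and 502 randomised patients are unchanged.

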### 3.3 Follow-up schedule

- (1) Face-to-face visit: day of randomization, 36 hours ( $\pm 12$  hours), 7 days ( $\pm 1$  day) /at discharge whichever is earlier
- (2) Telephone visit: 30 days ( $\pm 3$  days), 90 days ( $\pm 7$  days), and 12 months  $\pm 14$  days

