## 21. Appendix

**Appendix Table 1. Modified Rankin Scale**

The modified Rankin Scale (mRS) is an ordinal hierarchical scale ranging from 0 to 5, with higher scores indicating more severe disability. A score of 6 has been added to signify death.

| Category | Short description            | Long description                                                                                                                                |
|----------|------------------------------|-------------------------------------------------------------------------------------------------------------------------------------------------|
| 0        | No symptoms                  | No symptoms                                                                                                                                     |
| 1        | Symptoms, no disability      | Minor symptoms that do not interfere with lifestyle                                                                                             |
| 2        | Slight disability            | Slight disability, symptoms that lead to some restriction in lifestyle, but do not interfere with the patient's capacity to look after himself. |
| 3        | Moderate disability          | Moderate disability, symptoms that significantly restrict lifestyle and prevent totally independent existence                                   |
| 4        | Moderately severe disability | Moderately severe disability, symptoms that clearly prevent independent existence though not needing constant attention                         |
| 5        | Severe disability            | Severe disability, totally dependent patient requiring constant attention day and night.                                                        |
| 6        | Death                        | Death                                                                                                                                           |

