The planned sample size is 502 cases, and two analyses will be conducted when the 90-day follow-up of 1/3 (168 cases) and 2/3 (336 cases) of the total sample size is completed, and the study may be terminated in advance based on clear validity or ineffectiveness. The expected duration of each subject's enrollment is approximately 1 year. Subjects will be followed with assessments at 36 (24-48) hours, hospital discharge (or  $7 \pm 1$  days),  $30 \pm 3$  days,  $90 \pm 7$  days and 12 months  $\pm 14$  days post randomization.

A blinded core laboratory will assess baseline imaging to confirm vessel occlusion

---

and determine ASPECT score, 36 (24-48) hours post-randomization to assess presence of ICH, and to measure core infarct volume and determine angiographical variables such as final reperfusion status and residual stenosis.

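### SAP section 10 excludes patients with no post-randomisation visit, against the all-randomised FAS, and read literally would drop deaths before the 24–48 h visit

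*Supplement*

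**What the plan says.** Three parts of SAP v2.0 bear on who is analysed.

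- Section 10, Premature Withdrawal and Missing Data: "Subjects who do not attend any visits after randomization will be excluded from analysis of any endpoint, as no post-baseline data will be available". The rule covers every endpoint and makes no exception for death. The same section uses complete data without imputation for the main primary analysis, with LOCF and worst-case imputation as sensitivity analyses.
- Section 7, Full Analysis Set: "all randomized subjects, either treated with medication or with EVT will be included in the full analysis set". No visit is required. This is the primary efficacy population.
- Section 12, Main Model: "Based on an intention-to-treat basis, an ordinal logistic regression model with site as a random effect will be used".

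On timing, SAP section 5 says: "Subjects will be followed with assessments at 36 (24-48) hours, hospital discharge". Protocol V7.1 section 3.3 agrees: "Face-to-face visit: day of randomization, 36 hours" is how its visit list begins, and the schedule in section 8.6 labels the day of randomisation as baseline.

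On death, Protocol V7.1 Appendix Table 1 says of the mRS: "A score of 6 has been added to signify death". SAP section 13 analyses 90-day all-cause mortality with a Cox model in the safety set. Section 7 limits that set to "all subjects who received treatment with at least one time evaluation of safety outcome".

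**The concern.** A patient who dies before the 36-hour assessment has attended no scheduled visit after randomisation. Under section 10 that patient leaves every analysis; under sections 7 and 12 the patient stays, with an mRS of 6. The SAP gives no order of precedence, so two programmers following it faithfully could produce different primary denominators.

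The reason given for the exclusion, that nothing was observed after baseline, is untrue of a death. The patient's 90-day mRS is known, the mortality event has a date, and the 36-hour NIHSS response was not achieved. Protocol sections 9.2.2 and 9.3 make a death a serious adverse event that must be recorded.

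Applied literally, the rule is a post-randomisation exclusion on the worst outcome, in an open-label trial of an acute procedure. If the arms differ in very early deaths, the comparison tilts towards the arm that has more of them.

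**Working it through.** **1. Two rules for the same patient.** Take a patient who is randomised, dies at 12 hours, and has no assessment that anyone recorded as a visit.

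| Question | Section 10, literal | Sections 7 and 12 |
|---|---|---|
| In the primary mRS analysis? | No | Yes, mRS 6 |
| In the 90-day mortality analysis? | No | Section 7 leaves it open whether the death counts as a safety evaluation |
| In the 36-hour NIHSS analysis? | No | In the FAS; scoring not stated |

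The LOCF and worst-case analyses do not clearly rescue this patient, because the rule excludes the patient rather than leaving a missing value.

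**2. The plan's own sample size.** Inputs from SAP section 6: control mRS 0–6 of 3, 4, 10, 17, 16, 12 and 38%; common OR 1.73; two-sided alpha 0.046; power 0.90; 1:1 allocation; 10% attrition.

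Multiplying the control cumulative odds by 1.73 gives the EVT distribution. For death: 0.62/0.38 × 1.73 = 2.823, and 1 − 2.823/3.823 = 26.2%. The full EVT distribution is 5.08, 6.44, 14.64, 20.96, 16.25, 10.47 and 26.16%.

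N = 12(z₁ + z₂)² / [ln(OR)² (1 − Σp̄³)], where p̄ is the mean of the two arms' category probabilities, z₁ = 1.995 and z₂ = 1.282. This gives 450.3, so 451 (plan: 452), and 451/0.9 rounds up to 502 (plan: 502). The plan's figures are reproduced and are not in dispute.

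**3. Effect of the literal rule.** The documents give no rate of death before the first visit, so the shares below are assumptions. If a share e of an arm dies before the visit and the arm's 90-day mortality is d, analysed mortality becomes (d − e)/(1 − e), and every other category p becomes p/(1 − e). A proportional-odds model is then refitted to the two altered distributions. Each 1% is 251 × 0.01 = 2.5 patients per arm.

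| True effect | Assumed early deaths, BMM / EVT | Removed, BMM / EVT | Common OR | Analysed mortality, BMM / EVT |
|---|---|---|---|---|
| None | equal: 1, 2 or 5% each | 2.5, 5.0 or 12.6 each | 1.00 | equal |
| None | 1% / 3% | 2.5 / 7.5 | 1.04 | 37.4% / 36.1% |
| None | 2% / 5% | 5.0 / 12.6 | 1.07 | 36.7% / 34.7% |
| None | 3% / 1% | 7.5 / 2.5 | 0.96 | 36.1% / 37.4% |
| OR 1.73 | none removed | 0 / 0 | 1.73 | 38.0% / 26.2% |
| OR 1.73 | 1% / 1% | 2.5 / 2.5 | 1.74 | 37.4% / 25.4% |
| OR 1.73 | 5% / 5% | 12.6 / 12.6 | 1.79 | 34.7% / 22.3% |
| OR 1.73 | 1% / 3% | 2.5 / 7.5 | 1.84 | 37.4% / 23.9% |
| OR 1.73 | 3% / 1% | 7.5 / 2.5 | 1.68 | 36.1% / 25.4% |

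Worked line, no true effect, 1% / 3%: BMM (0.38 − 0.01)/0.99 = 37.4%; EVT (0.38 − 0.03)/0.97 = 36.1%.

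**4. False-positive rate for that line.** Analysed n = 502 × (1 − 0.02) = 492. The shift in the test statistic is ln(OR) × √[n(1 − Σp̄³)/12] = 0.256. The rejection probability is 1 − Φ(1.995 − 0.256) + Φ(−1.995 − 0.256) = 4.1% + 1.2% = 5.3%, against 4.6% nominal. With 2% / 5% the same calculation gives 6.3%. Both ignore the interim looks.

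**The case against.** The best defence is that the sentence was never meant for deaths. It stands under a heading about withdrawal and missing data, follows a sentence about patients who withdraw, and rests on there being no post-baseline data. A recorded death is post-baseline data: it is an mRS of 6, a Cox event, and a serious adverse event with a narrative in the study report. A reader might infer from the sentence that the plan removes early deaths. The documents do not say so, and that part of the defence stands. It does not remove the conflict: the exclusion sentence, unlike the one before it, is not confined to withdrawals, and no text exempts deaths.

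A second tempting inference is that fatal early bleeds vanish from the sICH analysis. The documents do not support it. The definition in Protocol Appendix Table 5 needs haemorrhage seen on imaging, with clinical worsening or a major intervention, so a classified sICH already carries post-baseline data. Section 8.5 also provides for unscheduled visits with NIHSS and mRS. Nor does the safety set plainly repeat the problem: it asks for a safety evaluation, not a scheduled visit, and death is itself a listed safety endpoint. What remains is that the SAP does not define what counts as an evaluation.

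Third, for a patient alive with no contact, the rule changes nothing in the main analysis, which uses complete data anyway. That is correct.

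Finally, a bias in favour of EVT cannot be inferred. It needs more very early deaths under EVT, and the documents give no figure for either arm.

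**Conclusion.** The contradiction is real and stands in the current SAP: section 10 excludes patients whom sections 7 and 12 include. Read literally, it would take deaths before the first scheduled visit out of the primary mRS and 90-day mortality analyses although those outcomes are known. Because it is a stated rule, it can produce a wrong result if followed.

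The size and direction of any bias are unknown. With equal early-death shares there is no bias under the null, and assumed shares of 1–5% move the planned OR only from 1.73 to 1.74–1.79. With unequal shares the bias favours the arm with more early deaths: a null OR of about 1.04 at an assumed 3% EVT against 1% BMM, and 0.96 with the shares reversed. The null cases also assume that 90-day mortality is the same in both arms, so an excess of early deaths is offset later. The finding concerns the mRS and mortality analyses; it does not extend to a claim that sICH events are lost.

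**What to change.** Delete the sentence in SAP section 10 and state instead:

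- all randomised patients are in the FAS, by allocated arm;
- any death up to the 90-day assessment is scored mRS 6 and counted as a mortality event, whether or not a visit took place;
- death before the 36-hour assessment is non-response for the NIHSS endpoint;
- a patient alive with no contact is missing, not excluded, and so enters the missing-data sensitivity analyses.

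For the safety set, add that a recorded death, or an event found at an unscheduled assessment, counts as a safety evaluation. The pre-specified safety set need not be replaced for sICH.

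The cost is a few lines of SAP text. No new data are needed, and the planned 452/502 patients and OR of 1.73 do not change. If early deaths occur, the arm that has them will look less favourable than under the literal rule.
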